#### Statistical Analyses

Descriptive statistics will examine treatment acceptability outcomes as well as the trial recruitment rate. A 2-tailed *t* test will be used to compare the treatment arms in terms of baseline characteristics, assessing randomization success. A mixed model design using the MIXED procedure in SAS (version 9.4; SAS Institute) applying an intent-to-treat approach will compare the intervention arm to the waitlist control group in terms of FertiQoL, PHQ-9, GAD-7, Copenhagen Multi-Center Psychosocial Infertility Fertility Problem Stress Scale, and Relationship Assessment Scale (RAS) score across the 9 outcome measurement points (ie, at the end of intervention week 7 and biweekly for 16 weeks). Each outcome will be examined in a separate model; subject will be treated as a random effect, and the treatment assignment will be treated as a fixed effect. A repeated statement will identify assessment week as a repeated measure factor. Baseline levels of the outcome will be included as a covariate. This method has been shown to provide optimal statistical power relative to measuring pre- and postintervention outcome change [36]. In using all available data, a mixed model design has also been shown to outperform ad hoc approaches, such as the last-outcome-carried-forward approach [37].

In addition to examining the main effect of treatment assignment on outcomes, the interaction between assignment and assessment week will be examined to determine whether outcomes are maintained across the 9 postintervention measurements. Sensitivity analyses will use a similar approach to examine potential treatment moderators: membership in the LGBTQIA+ communities, baseline FertiQoL score, cultural background, disability status, and pursuit of conception through medical intervention.

The LOGISTIC procedure will assess the occurrence of mood (major or minor depressive episode or persistent depressive disorder) and/or anxiety disorders (generalized anxiety disorder, social anxiety disorder, or panic disorder) in the 2 treatment arms at the posttreatment assessment as well as at the 16-week follow-up.

To limit the family-wise error rate, the Benjamin and Hochberg [38] false discovery rate correction will be applied to all analyses.

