#### Power Calculations

Power calculations were performed using G*Power (Axel Buchner) and are focused on the primary outcome, infertility-related quality of life. Based on SDs observed in the population of distressed women with infertility [18], setting α at .05 and power at 80%, a total of 128 participants would be needed to detect a moderate effect size (Cohen *f*=0.25), equivalent to a 6-point difference on the FertiQoL (out of 100) between 2 arms. To allow for a 25% (42/170) dropout rate, we will recruit 170 participants (85 per arm), in line with average completion rate of 82% observed in our meta-analysis of psychological interventions for infertility-related distress and allowing for additional drop-out given considering the 16-week follow-up.

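### The Benjamini-Hochberg rule for all analyses does not limit the family-wise error rate, and it puts the primary FertiQoL test under a stricter threshold than the alpha of .05 used for the sample size

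*Protocol article*

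**What the plan says.** The multiplicity rule is one sentence at the end of Statistical Analyses: "To limit the family-wise error rate, the Benjamin and Hochberg [38] false discovery rate correction will be applied to all analyses". No analysis is exempted. The same section plans:

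- a treatment effect for each of five scales (FertiQoL, PHQ-9, GAD-7, the Copenhagen stress scale and RAS);
- arm-by-week interactions;
- five moderators;
- logistic analyses of mood and anxiety disorders at two time points.

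Power Calculations says that the calculations "are focused on the primary outcome, infertility-related quality of life". It continues: "setting α at .05 and power at 80%, a total of 128 participants would be needed to detect a moderate effect size" (Cohen f = 0.25), "equivalent to a 6-point difference on the FertiQoL (out of 100) between 2 arms". Recruitment is set at 170 to allow for 25% dropout. Nothing there refers to the multiplicity correction.

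**The concern.** Two things do not fit together.

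First, the stated aim and the chosen procedure differ. Family-wise error is the probability of at least one false rejection. The false discovery rate is the expected share of false rejections among all rejections. BH bounds the second. It bounds the first only if no tested effect is real, which is not what the investigators expect. The Results part of the abstract predicts benefit on all mental health parameters, and equal effectiveness by LGBTQIA+ membership, cultural background and disability status. Significance of the Study predicts moderate to large effects. So the trial expects a mix of real effects and nulls.

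Second, the primary test sits inside the correction while the sample size treats it as standing alone at .05. Under BH its threshold moves with the other p-values, so a moderator result can decide whether FertiQoL counts as positive. The stated 80% power assumes that this cannot happen.

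**Working it through.** **Inputs from the article.** Alpha .05, power 80%, f = 0.25, 128 evaluable participants (64 per arm), 170 recruited. For two arms d = 2f = 0.5, and a 6-point difference then implies SD = 6/0.5 = 12.

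**Reproducing the stated size.** A two-sided two-sample t test at .05 with d = 0.5 and 64 per arm has power 80.1% (63 per arm: 79.5%), so N = 128 is confirmed. Dropout: 128/0.75 = 171 against 170 planned, and 42/170 = 24.7%. The stated figures hold for one test at .05.

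**Family size (assumed, because the article does not fix it).**
- m = 5: treatment effect on five scales.
- m = 10: plus five arm-by-week interactions.
- m = 12: plus two logistic tests.
- m = 37: plus 5 moderators × 5 scales = 25.

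**Threshold.** BH at q = .05 orders the p-values and rejects the k smallest, where k is the largest rank with p(k) ≤ .05k/m. A test that is rejected therefore meets a threshold between .05/m and .05. The threshold reaches .05 only when every test in the family is rejected.

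**Power at the strictest threshold, .05/m (t test, 64 per arm, d = 0.5).**

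| m | .05/m | Power | Evaluable N for 80% |
|---|---|---|---|
| 1 | .05 | 80.1% | 128 |
| 5 | .0100 | 58.5% | 192 |
| 12 | .0042 | 46.7% | 224 |
| 37 | .00135 | 33.2% | 268 |

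**Power of the primary test under BH itself.** Simulated normal test statistics with mean d√32 (since √(64/2) = √32), the five scales correlated 0.5, and all other tests independent nulls:

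| m | All five scales at d = 0.5 | Only FertiQoL at d = 0.5 |
|---|---|---|
| 5 | 76% | 60% |
| 10 | 66% | 51% |
| 12 | 64% | 49% |
| 37 | 48% | 36% |

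**Family-wise error under BH.** Same set-up with all five scales at d = 0.8. The probability of at least one false rejection among the nulls is 14% (m = 10), 16% (m = 12) and 22% (m = 37). The false discovery rate stays below 5% throughout. When every null is true, the simulated family-wise rate is .039 to .051 for m = 5 to 37, so BH delivers family-wise control only in that weak sense.

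**The planned model.** Take nine post-intervention measurements with equal pairwise correlation ρ, baseline correlation r with each of them, and a constant effect. The adjusted variance of the mean, in SD² units, is (1 + 8ρ)/9 − r², and the effective d is 0.5 divided by its square root. The article gives neither ρ nor r, so these are assumptions:

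| ρ, r | Variance | Power at .05 | at .05/12 | at .05/37 |
|---|---|---|---|---|
| .7, .6 | 0.373 | 99.6% | 95% | 91% |
| .7, .5 | 0.483 | 98% | 87% | 78% |
| .8, .4 | 0.662 | 93% | 71% | 58% |

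**The case against.** The strongest reply concerns size. The 36% to 76% figures belong to the simple two-group comparison, not to the baseline-adjusted model over nine measurements that will be fitted. As the last table shows, that model can keep power near or above 80% even at the strictest threshold, under plausible but assumed correlations. This stands as a limit on the magnitude. It does not reconcile the two sections: Power Calculations claims 80% at .05 for a single test and does not present the model's efficiency as a reserve for multiplicity.

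The family size is also open. The rule could mean BH within each set of tests, the 25 moderator tests presume every moderator on every scale, and defining the family is often left to an analysis plan. That also stands, and it is why the loss is given as a range. If many effects are real the loss is small: with seven main tests all at d = 0.5, power is 76% to 78%. The scenario in which only FertiQoL responds runs against the investigators' own expectations.

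A reader might go further in four ways that the article does not support:

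- **That there is no family-wise protection at all.** Weak control exists; strong control is what is missing.
- **That the primary result is more likely to be a false positive.** It is not: the BH threshold never exceeds .05, so the rule is conservative for that test.
- **That the baseline t tests, planned to "compare the treatment arms in terms of baseline characteristics, assessing randomization success", enlarge the family.** Only a very literal reading includes them, and no figure here does. Their usefulness is a separate reporting matter.
- **That the "Copenhagen Multi-Center Psychosocial Infertility Fertility Problem Stress Scale" is an unplanned outcome.** It is absent from the list under Secondary Outcomes, but Trial Design names infertility-related distress as something to be assessed. It is a side issue here.

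**Conclusion.** The point holds, and should be fixed. Two things are firm and need no assumption: the article attributes to BH an error rate that it does not control when some effects are real, and it leaves the primary test inside a correction that the sample size ignores. The harm is possible loss of power and a primary conclusion that can turn on exploratory p-values.

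The sizes are conditional. A family-wise error of 14% to 22% rests on five real effects of d = 0.8 and 10 to 37 tests. Primary power of 36% to 76% in place of 80% rests on the two-group comparison with m between 5 and 37 and either one or five real effects. To read these as the power of the planned analysis would go beyond the documents. That power cannot be fixed without the within-person correlations and the family, neither of which is given.

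**What to change.** Test the FertiQoL treatment effect once, at two-sided .05, outside any family. The stated alpha, the 128 evaluable participants and the 80% power then apply as written.

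Apply BH at q = .05 to a listed family of secondary treatment comparisons: PHQ-9, GAD-7, RAS, the Copenhagen scale if it is kept and named as an outcome, disorders at each time point, and health care use. Describe this as false discovery rate control. If family-wise control is what is meant, use Holm on the same list.

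Report moderator and arm-by-week tests as exploratory estimates with confidence intervals.

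The cost is wording only, with no change to sample size or data collection. The family must be settled before outcome data are analysed, since choosing it after seeing p-values would undermine the primary claim.

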#### Power Calculations

Power calculations were performed using G*Power (Axel Buchner) and are focused on the primary outcome, infertility-related quality of life. Based on SDs observed in the population of distressed women with infertility [18], setting α at .05 and power at 80%, a total of 128 participants would be needed to detect a moderate effect size (Cohen *f*=0.25), equivalent to a 6-point difference on the FertiQoL (out of 100) between 2 arms. To allow for a 25% (42/170) dropout rate, we will recruit 170 participants (85 per arm), in line with average completion rate of 82% observed in our meta-analysis of psychological interventions for infertility-related distress and allowing for additional drop-out given considering the 16-week follow-up.

#### Planned Recruitment Rate

We propose to complete the trial within 2 years. The timeline relies on a recruitment rate of 3 participants per week, which we consider to be a highly conservative estimate of what is possible based on our previous experience successfully recruiting participants from this population.

Through our experience in our preliminary work, we have determined that the most successful strategy for recruiting the target population is to advertise through online infertility support or special interest groups—this will therefore be the primary method used to recruit for this study. We have found these groups to be very willing to share our research, and their members are extremely receptive as well as highly likely to be eligible to participate. We have also had great success in recruiting individuals from LGBTQIA+ communities attempting to conceive through IVF. In an ongoing study specifically targeting this population, we approached a pair of social media influencers (a lesbian couple who regularly share their experiences of undergoing IVF) who enthusiastically shared our project with their followers. Within 2 days, we had received over 400 entries in our eligibility survey.

In addition to providing large pools of highly engaged, eligible participants, one important advantage of web-based recruitment is that samples tend to be much more diverse in terms of race, education, and income relative to studies that recruit through fertility clinics, the patients for which are disproportionately high-income. While web-based recruitment can increase the risk of recruiting noneligible individuals posing as eligible participants, the use of a face-to-face Zoom enrollment session greatly reduces this risk. Our research team is also experienced in identifying suspicious survey responses.

### Ethical Considerations

This study has been reviewed and approved by the University of Regina Ethics Board (REB #2023-210) as well as registered on ClinicalTrials.gov (NCT06006936). All prospective participants will provide informed written consent before enrolling in the trial.

To protect participant confidentiality, all participant data, including both interview data and questionnaire data, will be saved under ID numbers only, with no identifying information attached. Only the research team will have access to the collected survey data. The team will maintain a document associating participant names with their anonymous subject numbers. This document will be password-protected, opened only on encrypted devices, and stored separately from the rest of the data.

Participants will receive US $10 for each postintervention and follow-up survey completed and US $20 for each of the 2 postintervention interviews, for a maximum total of US $130.

## Results

Recruitment will begin in January 2024 and continue for approximately 1.5 years. All data are expected to be collected by January 2026. Results will be uploaded on the ClinicalTrials.gov website shortly thereafter.

## Discussion

### Significance of the Study

It is expected that participants assigned to the Coping with Infertility program will exhibit improved fertility quality of life as well as depressive and anxious symptoms, with moderate to large effect sizes. We also expect rates of clinical mood and anxiety disorders as well as self-reported health care use to be lower among participants randomized to the treatment arm. Baseline fertility quality of life is furthermore expected to moderate the effect of treatment such that effect sizes will increase with decreasing baseline fertility quality of life. Based on the pilot study results, we expect adherence and retention to be favorable. If our hypotheses are confirmed, these findings would suggest that the Coping with Infertility program is more effective than currently available psychological interventions for infertility. Indeed, a recent meta-analysis by our team identified 58 randomized controlled trials testing psychological interventions for infertility and found that, with the exception of trials conducted in the Middle East, interventions were associated with only small psychological benefits, highlighting the need for more effective interventions [16]. The self-help nature of the Coping with Infertility program also likely makes it more cost-effective than individual psychotherapy, which typically costs US $100-$200 per session.

If our intervention proves effective, we will aim to make our mobile app publicly available through the Apple Store and Google Play Store. Decreased health care use in the treatment arm relative to the treatment-as-usual arm would provide a strong rationale for seeking government funding to upkeep the Coping with Infertility mobile app, which would allow us to make the program available free of charge. We would provide flyers and posters to fertility clinics across North America, to be posted in clinic waiting rooms and physician offices. We will reach out to relevant professional societies and nonprofit organizations, asking them to include the app as a mental health resource listed on their website. Online forums relevant to infertility will also be contacted and asked to share information related to the app. A YouTube channel will be created to house all of the weekly module videos along with a professionally produced animated explainer video introducing the intervention and describing the results from the trial supporting its efficacy. Final, we will publish our findings in open-access journal articles in respected scientific journals.

In addition to disseminating the Coping with Infertility program as a stand-alone intervention, it may also be worthwhile to pair it with other traditional mental health resources. For example, future research pairing the Coping with Infertility program with infertility support groups, or with individual psychotherapy may help target a broader audience of individuals experiencing infertility-related distress who wish to benefit from peer or therapist support. Translating the content of the program into a workbook format may also appeal to a subset of the target population.

### Limitations

First, access to the Coping with Infertility program is contingent upon internet access; research participants may therefore not include individuals who do not have such access, such as those who cannot afford internet access or those living in remote communities. Second, due to the nature of the intervention, it is impossible to conduct this trial as a double-blind, randomized trial. Third, health care use will be self-reported and therefore may not capture use as accurately as hospital and clinic records.

### Conclusions

This study will test a self-help program for infertility-related distress through a mobile app. If the intervention proves effective, it will provide a highly cost-effective and accessible mental health resource for those struggling with the mental health impacts of infertility. This will fill an important gap in light of high rates of psychopathology among those experiencing infertility and considering the current lack of effective psychotherapy approaches for infertility.

## Appendix

Multimedia Appendix 1 Peer review report from the Canadian Institutes of Health Research.

## Abbreviations

CONSORT-SPI: Consolidated Standards of Reporting Trials for Social and Psychological Intervention Trials
DSM-5: Diagnostic and Statistical Manual of Mental Disorders, Fifth Edition
FertiQoL: Fertility Quality of Life Scale
GAD-7: Generalized Anxiety Disorder-7
ICC: internal consistency coefficient
IVF: in vitro fertilization
LGBTQIA+: lesbian, gay, bisexual, transgender, queer, intersex, and asexual
PHQ-9: 9-item Patient Health Questionnaire
PRIME-MD: Primary Care Evaluation of Mental Disorders
SCID: Structured Clinical Interview for the DSM-5
